#### Feasibility of Delivering the CliMACT Training

The feasibility of delivering the CliMACT training will be assessed at the posttraining assessment based on the criteria as delineated in the following. Satisfaction is measured through 3 scales. A 21-item participant debriefing questionnaire with a 7-point Likert scale ranging from 1-7, with higher values indicating higher satisfaction [16]. The 6-item perceived impact subscale of the Mobile App Rating Scale has a 6-point scale ranging from 0-5, with higher scores indicating higher perceived helpfulness. Lastly, there will be one item reflecting a global 5-star rating of the application, ranging from 1-5 [44].

Participant adherence is measured using the number of attended sessions and the number of completed consolidating and adaptive EMI components during training.

Fidelity to the training protocol is measured using a 19-item session component checklist adapted to CliMACT training components from the study by Reininghaus et al [16] with a yes-no format, and the 25-item Acceptance and Commitment Therapy Fidelity Measure with a 4-point scale ranging from 0-3 [45], with higher values indicating greater frequency of behavior aligned with ACT principles. Measures are completed by the mental health professional delivering the face-to-face session and by an independent rater. As active ingredients, CliMACT training components will be assessed as specific ingredients, and working alliance with the mental health professional and with the digital tool are measured as nonspecific ingredients, using the 12-item Working Alliance Inventory with a 5-point Likert scale ranging from 1-5 (Working Alliance Inventory-Self Report [WAI-SR]) [46,47] and 25-item Mobile Agnew Relationship Measure with a 7-point Likert scale ranging from 1-7 [48], with higher scores indicating a more positive working alliance for both measures.

#### Candidate Outcomes

As candidate outcomes, participants will complete the following self-report measures at baseline, post training, and 4-week follow-up: mental well-being is measured using the Warwick-Edinburgh Mental Well-Being Scale with 14 items using a 5-point Likert scale ranging from 1-5 [49,50]. The total score is a sum score, with higher scores indicating better mental well-being. Quality of life is measured using the World Health Organization Quality of Life measure with 26 items using a 5-point Likert scale ranging from 1-5 [51,52]. In the current study, the subscales for psychological health (6 items) and social relationships (3 items) will be considered as candidate outcomes. Domain scores are transformed to a scale from 0-100, with higher values indicating a higher quality of life. Subjective happiness is measured using the Subjective Happiness Scale with 4 items using a 7-point Likert scale ranging from 1-7 [53,54]. Reversing one negatively formulated item, a mean score is calculated, with higher scores indicating higher happiness. Climate change distress, used both as a screening and an outcome measure, is measured using the CC-DIS, with 15 items reflecting distress and 8 items reflecting impairment, using a 5-point Likert scale ranging from 1-5 [3]. After reversing items that indicate low levels of distress or impairment, a mean score is calculated, with higher scores indicating higher distress and impairment. General psychological distress is measured using the Core 10, a 10-item measure using a 5-point Likert scale ranging from 0-4 [55] and the Brief Symptom Inventory, a 53-item measure using a 5-point Likert scale ranging from 0-4 [56,57], with higher mean scores indicating higher psychological distress.

Using EMA (movisensXS app, movisens GmbH), 18 items are used to assess momentary affect on a Visual Analog Scale (VAS) ranging from 0-100. In this study, the mean of 4 unipolar positive affect facet items will be used as the total positive affect score. The mean of 9 unipolar negative affect items will be used as the total negative affect score. Based on the CC-DIS [3], 6 items are used to measure momentary climate change distress (3 items) and impairment (3 items), using a 7-point Likert scale ranging from 1-7. Mean scores will be used as scale scores. During the training phase, participants in the experimental condition complete an abbreviated EMA form in the InteractionDesigner platform, including 11 items assessing momentary affect on a 7-point Likert scale and a multi-select item to indicate which specific affects are currently related to climate change. All EMA items can be found in Multimedia Appendix 3.

#### Candidate Mechanisms

As candidate mechanisms, participants will complete the following measures at baseline, post training, and 4-week follow-up: self-efficacy is measured using the General Self-Efficacy Scale with 10 items using a 4-point scale ranging from 1-4 [58,59]. A sum score is calculated, with higher scores indicating higher levels of self-efficacy. Emotion regulation is measured using the Cognitive Emotion Regulation Questionnaire with 18 items using a 5-point Likert scale ranging from 1-5 [60,61]. First, subscale items are summed. Next, a mean score of 5 subscales is calculated for the adaptive emotion regulation scale, and a mean score of 4 subscales is created for the maladaptive emotion regulation scale. Resilience is measured using the Connor-Davidson Resilience Scale with 25 items using a 5-point Likert scale ranging from 0-4 [62,63]. The total score is a sum score, with higher scores indicating higher resilience. Self-compassion is measured using the Self-Compassion Scale with 26 items using a 5-point Likert scale, ranging from 1-5 [64,65]. Negatively formulated items are reversed, means for subscales calculated, and then subscale scores summed for the total score, with higher scores indicating higher levels of self-compassion. Mindfulness is measured using the Five-Facet Mindfulness Questionnaire with 24 items using a 5-point Likert scale ranging from 1-5 [66,67]. Facet scores are computed as sum scores (observing: 4 items; describing: 5 items, acting with awareness: 5 items; nonjudging of inner experience: 5 items, and nonreactivity to inner experience: 5 items. Psychological inflexibility is measured using the Acceptance and Action Questionnaire II with 7 items using a 7-point Likert scale ranging from 1-7 [68,69]. The total score is a sum score, with higher scores indicating higher psychological inflexibility. Internalized stigma is measured using an adapted version of the Internalized Stigma of Mental Illness scale with 29 items using a 4-point scale ranging from 1-4 [70,71]. The measure covers alienation (6 items), stereotype endorsement (7 items), discrimination experience (5 items), social withdrawal (6 items), and stigma resistance (5 items). A mean score is calculated as the total score, excluding the stigma resistance subscale [72]. Experiences of discrimination are measured with the adapted version of the major experiences of discrimination measure [73], using a multi-select item asking about the experience of unfair treatments in different areas (police, judicial system, discouraging education, neighbors and family, service, medical attention, public transport, school, superiors, and other) due to the participants’ climate change–related attitudes, views and actions. For areas in which unfair treatment is reported, participants can indicate the number of times this has occurred. The total number of experiences is used as the total score. Self-stigma of seeking help is measured using the Self-Stigma of Seeking Help Scale with 10 items using a 5-point Likert scale ranging from 1-5 [74]. Reversing positively phrased items, a sum score is used as the total score, with higher values indicating higher self-stigma. PEB is measured using an adapted and translated version of the PEB measure with 18 items using a VAS ranging from 0-100 [75]. Mean scores are calculated for personal behavior (10 items) and collective behavior (8 items), with higher scores indicating more opportunities at which the participant has engaged in PEBs.

Using EMA, momentary self-efficacy is measured with 2 items based on the measure per Majeed et al [76] on a VAS ranging from 0-100. Positive and negative event intensity are respectively measured on a 7-point Likert scale ranging from 1-7. For negative event intensity ≥2, momentary emotional resilience is assessed using 1 item [12] on a VAS ranging from 0-100. Current activity is reported using a multi-select item, and for each confirmed activity, 1 of 10 matching momentary PEBs is queried on a VAS ranging from 0-100. Momentary value-based living is measured using 3 adapted items from the Engaged Living Scale [77] on a VAS ranging from 0-100. During the training phase, activity and events, but not momentary self-efficacy, PEB, or value-based living, will be assessed in daily EMA.

#### Measures for the Economic Evaluation

Two measures for the economic evaluation will be administered to assess health-related quality of life, use of care services, and the associated costs of care and service use. Health-related quality of life is measured using the EQ-5D-Y-3L instrument with 5 items using a 3-point Likert scale, ranging from 1-3, with higher scores indicating lower health-related quality of life, and 1 VAS item ranging from 0-100, with higher scores indicating better health [78,79]. The information on use of care services, which is needed to calculate the associated costs of care service use, is captured using an adapted version of the Client Service Receipt Inventory (CSRI) [80,81]. Together with other self-report measures of the trial, both measures for the economic evaluation (EQ-5D-3L and CSRI) will be administered at the 3 time points: at baseline, post training, and 4-week follow-up.

#### Other Measures

At each assessment, it will be documented if any adverse events (AEs) related or unrelated to the training or study participation have occurred, including health-related events, technical problems with the smartphone, problems with the digital application, or other issues. Marginalized or vulnerable group status is reflected by equity-relevant sociodemographic indicators at baseline and coded present when at least one of the following is true: female gender, ethnic minority, migration history, low family SES, current urbanicity, and lower education level. At posttraining, adverse trial effects are measured with the measure by Hutton et al [82], using a 5-point Likert scale ranging from 1-5. An overview of all measures and time points can be found in Figure 2 (in line with the SPIRIT [Standard Protocol Items: Recommendations for Interventional Trials] statement [83]).

**Figure 2 figure2:**
[figure not shown]
SPIRIT figure. AAQ-II: Acceptance and Action Questionnaire; ACT-FM: Acceptance and Commitment Therapy Fidelity Measure; AE: adverse events; ATE: adverse trial effects; BSI-53: Brief Symptom Inventory 53; CAU: care as usual; CC-DIS: Climate Change Distress and Impairment Scale; CD-RISC: Connor-Davidson Resilience Scale; CERQ: Cognitive Emotion Regulation Questionnaire; CliMACT+CAU: Climate - Mind and Act+Care as Usual; CSRI: Client Service Receipt Inventory; FFMQ: Five Facet Mindfulness Questionnaire; GSES: General Self Efficacy Scale; ISMI: Internalized Stigma of Mental Illness-Scale; mARM: Mobile Agnew Relationship Measure; MARS-G: Mobile App Rating Scale - German Version; MED: major experiences of discrimination; PEB: proenvironmental behavior; SCS-D: Self-Compassion Scale - German Version; SHS: Subjective Happiness Scale; SPIRIT: Standard Protocol Items: Recommendations for International Trials; SSOSH-10: Self-Stigma of Seeking Help; WAI-SR: Working Alliance Inventory - Self Report; WEMWBS: Warwick-Edinburgh Mental Well-Being Scale; WHO-QoLBref: World Health Organization Quality of Life - Brief Version; WHODAS 2.0: World Health Organization Disability Assessment Schedule 2.0.

### Randomization and Blinding

After completing baseline assessments, participants will be randomized at a 1:1 ratio to the experimental or control condition. Randomization will be performed by a nonblinded researcher training delivery team through a computer-generated sequence not accessible to blinded team members, applying block randomization with blocks of 5. Nonblinded researchers inform participants of their allocation. All outcomes will be assessed, and the statistical analysis will be performed, blind to random allocation. If unblinding occurs, this will be documented, and a different study team member will continue follow-up assessment for the respective participant.

In the experimental condition, a microrandomized trial (MRT) with repeated within-person randomization is implemented in the adaptive EMI components. Six CFI-based EMI components become available throughout weeks 1-3. If participants exceed the negative affect threshold (within-subject mean ±0.5 SDs) for triggering adaptive EMI components, participants will be randomized to receive a CFI-based EMI component they are already familiar with (ie, components that have been introduced as an enhancing EMI component) as experimental condition or no EMI component as control condition with a randomization ratio of 6:1. Repeated within-person randomization will be carried out via the InteractionDesigner platform.

### Justification of Sample Size

#### Feasibility RCT

The sample size for this feasibility RCT is primarily determined to address the primary objective to provide the basis for successful recruitment in a fully powered efficacy-effectiveness RCT. Initial sample size planning points to ≈180 participants required for the full RCT. To this end, we set a feasibility limit of a minimum monthly recruitment rate of 11 participants in (at least) the month with the highest recruitment rate of the feasibility trial recruitment period. This lower bound reflects the minimum monthly recruitment rate required to recruit an expected ≈180 participants for a subsequent fully powered RCT within a designated period of 17 months. This study’s population for the feasibility RCT will comprise a maximum of 50 youth aged 14-25 years (n=25 in the experimental and control conditions, respectively) with climate change–related distress. This upper limit of 50 is based on recommendations by Whitehead et al [84] for determining sample size for feasibility RCTs and would reflect a monthly recruitment rate of 17 if recruitment can be completed within 3 months. Thus, the feasibility trial will inform us about the feasibility of the aspired recruitment rate and the possibility of overrecruitment.

#### MRT Sample Size Calculation

To address the objective of exploring CliMACT training components as specific active ingredients, an MRT will be conducted. Based on the power approximation for MRTs [85,86], a sample size of 25 participants is sufficient to detect a small effect size of *d* ≥0.15 on a proximal EMA outcome, with *t*=252 decision points (based on our EMIs with a training duration of 42 days with 6 random EMA prompts per day) and a power of 80% for a 2-sided test α=.05, with an availability rate η (ie, proportion of completed EMA observations at given decision point T) of 50% and a randomization probability of 0.85 (ie, a ratio of 6:1 for experimental vs control components).

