##### Adaptive EMI Delivery Scheme

Participants’ responses to short, daily EMA questionnaires on momentary affect provide the basis for delivering CFI-based intervention via the adaptive EMI delivery scheme tailored to person, moment, and context. These are offered in moments of high negative affect, that is, when ratings exceed the threshold of an individual’s moving average on any negative affect item by ≥0.5 SDs. A prerequisite for the use of the moving average is that respondents have responded to at least 7 EMA prompts within the past 7 days. If this is not the case, a value of ≥4 on any negative affect item serves as a threshold for the adaptive EMI delivery scheme.

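### The microrandomized trial's power statement takes availability as prompt completion alone, although randomization also requires the negative-affect trigger, so 80% power for d=0.15 is not supported at the plan's own 50% completion

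*Protocol article*

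**What the plan says.** The section MRT Sample Size Calculation states that "a sample size of 25 participants is sufficient to detect a small effect size of" d "≥0.15 on a proximal EMA outcome". Its inputs are 252 "decision points (based on our EMIs with a training duration of 42 days with 6 random EMA prompts per day", "a power of 80% for a 2-sided test α=.05", a randomization probability of 0.85 (described as 6:1), and the design is computed "with an availability rate η (ie, proportion of completed EMA observations at given decision point T) of 50" per cent. Availability is thus defined there as completion of the prompt and nothing else.

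The section Randomization and Blinding makes randomization conditional: "If participants exceed the negative affect threshold (within-subject mean ±0.5 SDs) for triggering adaptive EMI components, participants will be randomized" to a familiar compassion-focused component or to none. It adds that "Six CFI-based EMI components become available throughout weeks 1-3". The section Adaptive EMI Delivery Scheme describes the trigger as a rating above the person's "moving average on any negative affect item by ≥0.5 SDs", with a fallback of a rating of 4 or more on any negative affect item when fewer than 7 prompts were answered in the past 7 days. The Feasibility part of the Statistical Analysis section likewise describes the MRT contrast as randomized only in moments of higher negative affect.

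**The concern.** In an MRT, availability is the share of decision points at which a person can actually be randomized. Here a completed prompt that does not trigger produces no randomization and adds nothing to the contrast. The calculation nevertheless counts every completed prompt. The effective availability is completion times the trigger probability given completion, times the chance that a component has already been introduced. With completion at 50%, that product is below 0.50 unless every completed prompt triggers.

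This is the article's only power statement. A reader would take from it that 25 participants suffice for a small proximal effect. If availability is lower, the precision of the MRT estimate is overstated. The article defines availability itself, so this is a stated input that conflicts with the stated design, not a detail left to the analysis plan.

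**Working it through.** **Inputs from MRT Sample Size Calculation:** n=25; T=42×6=252; η=0.50; d=0.15; two-sided α=0.05; randomization probability ρ=0.85 as written, or 6/7=0.857 from the 6:1 ratio.

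**Formula (assumed).** The article cites a power approximation for MRTs without printing it. I used the usual form with a constant effect and one baseline parameter:

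- noncentrality c = n·T·η·ρ(1−ρ)·d²
- power = P[F′(1, n−2; c) > F₀.₉₅(1, n−2)], here with 1 and 23 degrees of freedom

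**Step 1: reproduce the stated figure.**

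- ρ=6/7: c = 25×252×0.50×0.1224×0.0225 = 8.68, power 0.805, smallest n = 25
- ρ=0.85: c = 25×252×0.50×0.1275×0.0225 = 9.04, power 0.821, smallest n = 24

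The plan's 80% is therefore arithmetically right for η=0.50.

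**Step 2: how much slack is there?** Power of 0.80 needs c=8.56, which means η of at least 0.493 (ρ=6/7) or 0.474 (ρ=0.85). With completion at 0.50, the trigger must fire at 0.493/0.50 = 99% or 0.474/0.50 = 95% of completed prompts. A plain normal approximation is a little more generous. It needs c = (1.960+0.842)² = 7.85, so 7.85/8.68 = 90% or 7.85/9.04 = 87% of completed prompts.

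**Step 3: put the trigger into availability.** Set η = 0.50 × trigger rate, leave the other inputs unchanged, and use ρ=6/7. The protocol gives no trigger rate, so every rate below is an assumption.

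| Assumed trigger rate | η | Randomizations per person | Power for d=0.15 | d detectable with 80% power |
|---|---|---|---|---|
| 100% (implicit in the plan) | 0.500 | 126 | 0.805 | 0.149 |
| 89% | 0.445 | 112 | 0.76 | 0.158 |
| 75% | 0.375 | 94.5 | 0.69 | 0.172 |
| 60% | 0.300 | 75.6 | 0.59 | 0.192 |
| 50% | 0.250 | 63 | 0.51 | 0.211 |
| 31% (lower scenario) | 0.155 | 39 | 0.35 | 0.27 |

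Using ρ=0.85 instead adds 1 to 2 percentage points of power in each row.

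**Where the assumed rates come from.** For one normally distributed score, the chance of lying at least 0.5 SD above its mean is 1−Φ(0.5) = 0.31. Under a rule met by any of several items the rate is higher: simulating 5 to 9 normal items with inter-item correlation 0.2 to 0.6 gives about 60-89%. The simulation ignores the 7-point scale, the moving average and the fallback rule, and the article's text does not say how many of the 11 affect items in the training-phase form are negative. It indicates a range and is no more than that.

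**Step 4: what would rescue 80%?** Completion × trigger rate must be about 0.50: 100% completion at a 50% trigger rate, 83% at 60%, or 71% at 70%. Below a 50% trigger rate it cannot be reached.

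**The case against.** The strongest reply is that little depends on this figure. Under Justification of Sample Size, the trial's size rests on recruitment feasibility with a maximum of 50, so 25 in the experimental arm follows from that and not from the MRT. No traffic-light criterion uses MRT power, and data collection ended in August 2025. All of this stands and limits the point to a correction of an exploratory sub-analysis.

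A reader might also infer several stronger things that the documents do not support:

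- *That the MRT certainly lacked 80% power.* The trigger rate is unknown and actual completion may have exceeded 50%. At 70% completion and a 70% trigger rate, η=0.49 and power is again 0.80. The article claims neither figure, but it does not exclude them.
- *That power is as low as 0.35.* That needs a single roughly normal score, whereas the delivery scheme speaks of any negative affect item.
- *That the two threshold descriptions imply very different trigger rates.* The within-subject mean ±0.5 SD in Randomization and Blinding may be loose shorthand for the moving-average rule, and the same sentence speaks of exceeding the threshold. The wording needs aligning, but two different rules are not established.
- *That a null result will be read as excluding a small effect.* No section plans this. The MRT is described as exploratory, and the efficacy section promises confidence intervals and d-type effect sizes.
- *That attrition or late introduction of components costs a known further amount.* The documents give no MRT attrition figure, people who drop out contribute prompts until they leave, and only one familiar component is needed for randomization.

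**Conclusion.** The point holds as an internal inconsistency in an input. The arithmetic is right, but the definition of availability does not match the randomization rule. At the plan's own 50% completion the direction is certain: availability is below 0.50 unless every completed prompt triggers. The claim of 80% power for d=0.15 is then not supported, because it needs about 95-99% of completed prompts to trigger (87-90% under the normal approximation), which sits badly with a component reserved for moments of high negative affect.

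The size of the loss is not known. Across assumed trigger rates of 50-89%, power is 0.51 to 0.76 and detectable d is 0.211 down to 0.158, with 31% (power 0.35, d 0.27) only as a lower scenario. These figures rest on the constant-effect approximation, ρ=6/7, all 25 participants contributing, and a component always being available. Should be fixed; neither the trial's sample size nor its feasibility criteria are affected.

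**What to change.** In MRT Sample Size Calculation, define η as the proportion of decision points at which the prompt is completed, the trigger fires and a component has been introduced. State the assumed completion and trigger rates separately, the latter as a range. Replace the statement that 25 participants suffice for d≥0.15 at 80% power with the detectable d over that range, about 0.16 to 0.21 for trigger rates of 89% down to 50% at 50% completion, with 0.27 as a labelled lower scenario. Use one value for the randomization probability, since 6:1 is 0.857 and not 0.85.

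Reconcile the threshold wording in Adaptive EMI Delivery Scheme and Randomization and Blinding, and state which form the app used, because availability depends on it.

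If the trigger rate is taken from the collected data, pool it over MRT condition and label the result a retrospective precision statement, not an a priori justification.

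The cost is one recalculation, a few sentences and a less favourable figure. It needs no further participants and no change of design.

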As nonspecific active ingredients (objective 2 continued), we will explore the association of working alliance toward mental health professionals as well as working alliance with the app-based EMI with the 8 candidate outcomes in participants of the experimental condition, using linear mixed models. Separate models will be fitted for each alliance type and candidate outcome at both posttraining and 4-week follow-up; additionally, time (posttraining and 4-week follow-up), the respective outcome at baseline, and working alliance will be entered as independent variables (details set in preregistered statistical analysis plan, becoming public on OSF after publication of results) [87]. A level-2 random intercept for subject and a random effect for time will be added, and level-1 residuals will be allowed to be correlated to account for within-subject nesting of repeated measures. For the 2 momentary outcomes of nonspecific active ingredients, outcomes measured at baseline will be person-mean centered, and, in addition to the above specifications, random slopes for time and working alliance will be added, with an unstructured variance-covariance matrix. Within-subject residuals will be modeled with an autoregressive structure of the exponential type, allowing the models to account for unequally spaced time values. Restricted maximum likelihood estimation will be applied.

As specific active ingredients (objective 2 continued), we will explore proximal effects of CFI-based CliMACT training components on momentary negative affect in an MRT design in participants in the experimental condition using linear mixed modeling. MRT condition (experimental: any adaptive CFI-based training component vs control: no adaptive training component, randomized at a ratio of 6:1 in moments of higher negative affect), negative affect at *t*_n_ (person-mean centered), and time between assessment time points will be entered as independent variables. Negative affect at *t*_n+1_ will be entered as the dependent variable. A level-2 random intercept will be added, and level-1 residuals will be allowed to be correlated to account for within-subject nesting of repeated measures. Restricted maximum likelihood estimation will be applied.

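### The microrandomized trial's 80% power counts every completed prompt as randomized, although only prompts that meet the negative-affect trigger are

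*Protocol article*

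**What the plan says.** All references are to the protocol article.

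- **MRT Sample Size Calculation** states that "a sample size of 25 participants is sufficient to detect a small effect size" of d "≥0.15 on a proximal EMA outcome". The inputs are 252 decision points (42 days × 6 prompts), 80% power, two-sided α=.05, a randomization probability of 0.85 (6:1), and an "availability rate η (ie, proportion of completed EMA observations at given decision point T) of 50" per cent.
- **Adaptive EMI Delivery Scheme** says of the adaptive components: "These are offered in moments of high negative affect". The trigger is a rating above the person's "moving average on any negative affect item by ≥0.5 SDs". With fewer than 7 answered prompts in the past 7 days, a rating of 4 or more on any negative item is used instead.
- **Randomization and Blinding** makes the trigger a condition of randomization: "If participants exceed the negative affect threshold (within-subject mean ±0.5 SDs) for triggering adaptive EMI components, participants will be randomized".
- **Statistical Analysis, Feasibility** describes the control condition of the analysed contrast as "no adaptive training component, randomized at a ratio of 6:1 in moments of higher negative affect".
- **Candidate Outcomes** describes the training-phase form as "including 11 items assessing momentary affect on a 7-point Likert scale" and does not say how many of the items are negative.

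**The concern.** In a microrandomized trial, a decision point contributes to the treatment contrast only if the participant can be randomized there. Here that requires two things: the prompt is answered, and the answer meets the negative-affect trigger. The sample-size section allows for the first and not the second. No other input reduces the number of decision points for the trigger, so the information in the contrast is overstated by a factor of one over the trigger share.

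This calculation is the only support for calling 25 participants sufficient for the specific-active-ingredient objective. If fewer moments are randomized than planned, an imprecise or null estimate could be taken as evidence against the compassion-focused components when the design had limited ability to detect d=0.15.

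A smaller wording point sits beside this. The bracket in Randomization and Blinding gives the threshold as the within-subject mean ±0.5 SDs. The delivery-scheme section gives an upward rule on any item against a moving average, with a fallback. The upward direction is clear from the surrounding text, but the bracket misstates the rule.

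**Working it through.** **Inputs from the sample-size section:** N=25, T=252, η=0.50, d=0.15, two-sided α=0.05, randomization probability p=0.85. The stated 6:1 ratio is exactly 6/7=0.857, so both values are carried.

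**Formula.** Standard MRT power approximation with a constant effect: noncentrality λ = N × T × η × p(1−p) × d², referred to a noncentral F with 1 and N−2 = 23 degrees of freedom.

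**Step 1: reproduce the stated figure.** The completed moments are 25 × 252 × 0.5 = 3150.

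- p=6/7: λ = 3150 × 0.12245 × 0.0225 = 8.68, power 80.5%, N for 80% = 25.
- p=0.85: λ = 3150 × 0.1275 × 0.0225 = 9.04, power 82.1%, N for 80% = 24.

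The stated figure is reproduced, with all 3150 completed moments counted as randomized.

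**Step 2: include the trigger.** Let s be the share of completed prompts that trigger. Availability becomes η = 0.50 × s, and λ is multiplied by s.

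**Step 3: break-even.** Power equals 80% at s=0.986 (p=6/7) or s=0.947 (p=0.85). This step needs no assumption about the actual share.

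**Step 4: plausible values of s (assumption).** The article gives no trigger share.

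- For one normal item, P(at least 0.5 SD above its mean) = 0.31. The any-item rule raises this.
- For k equicorrelated normal items, the share is 0.56 with k=5 and correlation 0.7, and 0.84 with k=9 and correlation 0.3.
- A simulation closer to the stated rule gives 0.46 to 0.82. It used 4–7 seven-point items with means 1.5–3.5 and SD 1.2, 50% of 252 prompts completed, a 7-day moving average and SD, and the fallback of 4 or more.

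**Step 5: results with 50% completion, p=6/7** (power at p=0.85 in brackets).

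| Trigger share s | λ | Power for d=0.15 | d detectable at 80% | N for 80% |
|---|---|---|---|---|
| 1.00 | 8.68 | 80.5% (82.1%) | 0.149 | 25 |
| 0.84 | 7.29 | 73% (75%) | 0.163 | 29 |
| 0.70 | 6.08 | 66% (67%) | 0.178 | 35 |
| 0.56 | 4.86 | 56% (58%) | 0.199 | 43 |
| 0.46 | 3.99 | 48% (50%) | 0.220 | 52 |

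The single-item share of 0.31 would give 35% power. It is a low sensitivity value only, because the article's rule is any-item.

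**Step 6: control moments per person.** 252 × 0.5 × s ÷ 7 gives 18 at s=1, 15 at s=0.84 and 10 at s=0.56.

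**Step 7: completion that would offset the trigger.** Keeping 80% with 25 participants at 6:1 needs completion of 0.5 × 0.986 ÷ s. That is 59% at s=0.84, 70% at s=0.70 and 88% at s=0.56. At s=0.46 it exceeds 100%, so it cannot be reached.

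Two further restrictions are left out: only components already introduced can be delivered, and the outcome needs an answered next prompt. Both could only reduce the usable moments further.

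**The case against.** The strongest case against concerns size and consequence, since the mismatch itself is plain in the text.

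- **The size cannot be fixed from the article.** It depends on how many of the 11 training-phase items are negative, and on their distributions and correlations. This stands: the power values in the table are illustrations. The break-even in Step 3 does not depend on them.
- **The 50% completion rate is only a planning value.** If completion were higher, the loss could be made up. At 70% completion and a 70% trigger share, power is 80% (6:1) or 81% (0.85). This also stands, so a shortfall in the trial as conducted is not shown. But the article defines 50% as completion alone and nowhere says that it already includes the trigger.
- **The loss may be modest.** At a share of 84% the detectable effect is 0.163, still small. That is so at the favourable end; at 56% it is 0.199.
- **The analysis is exploratory.** Table 1 has no criterion tied to the MRT, the trial is sized on recruitment, and a confidence interval would show imprecision. This limits the consequence. It does not make the stated power correct.
- **Recomputing power from the observed share after data collection would be retrospective power.** This is fair. The confidence interval is the better guide to what the completed data can show, and the observed share is useful mainly as a description.

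**Conclusion.** The concern holds. The stated 80% power for d=0.15 with 25 participants treats availability as completion alone, which conflicts with a design that randomizes only at triggered moments. The direction is certain for any trigger that selects moments of higher negative affect: at 50% completion there is room for only 1% (6:1) to 5% (0.85) of completed prompts to miss the trigger.

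The size rests on an assumed trigger share. Over 56–84%, power at 6:1 is 56–73%, the detectable d is 0.163–0.199, and 29–43 participants would be needed. The seven-point simulation allows a share as low as 46%, with 48% power. All these values hold completion at 50% and use the constant-effect approximation that reproduces the article's own figure.

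The correction should be made, but its reach is limited to the exploratory MRT objective. Recruitment, randomization, retention and the other feasibility criteria are untouched.

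**What to change.** 1. In MRT Sample Size Calculation, define availability as the probability that a prompt is completed and the trigger is met.
2. Restate the power for d=0.15, or preferably the effect detectable with 80% power, over a stated range of trigger shares and at a stated completion rate.
3. When results are reported, give the observed trigger share and the number of randomized moments per condition from the platform's randomization log, and judge precision from the confidence interval.
4. In Randomization and Blinding, replace the bracketed threshold with a reference to the rule in Adaptive EMI Delivery Scheme.

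The cost is a wording change and one recalculated, less favourable figure. Trial conduct and data collection do not change.
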